iii) To calculate and compare (where relevant) the incidence of potentially avoidable serious early neonatal morbidity and perinatal mortality, overall, and 1) in women whose LMC is reported as being a midwife where there is no evidence of medical input, 2) in women whose LMC is reported as being a midwife where there is evidence of medical input and 3) in women whose LMC is a general practitioner or obstetrician.

Inclusion criteria

- Singleton pregnancy
- Delivered during a specified time period (likely to be 1^st^ January 2006 and 1^st^ January 2010, The final inclusion period will be based on DHB birthing numbers and required sample size)
- Birthed at one of six specified District Health Boards
- Equal to or greater than 37 weeks gestation
- No identified major fetal or neonatal congenital, chromosomal, or metabolic abnormalities.

The sample size has been determined based on power calculations using the rarest outcome in the study, intrapartum fetal death. Sample size has been calculated using the Fleiss method with continuity correction in OpenEpi. Outcome rates have been estimated based on the Dutch Perinatal Mortality Study. An adequately powered simple study requires a sample size of 48 878. However, we need to increase the sample size because we wish to adjust the results for several major confounders particularly maternal age, antenatal risk, ethnicity, deprivation and parity of the mother. Furthermore, we wish to perform some subgroup analysis. For these reasons, we plan to double the sample size.

Exposure

- Reference group

Women who are reported to have a midwife as Lead Maternity Carer at booking and at admission in labour and where there is no evidence of medical input.

- Comparison groups

Women who are reported to have a midwife as LMC with evidence of medical input. Women will be included in this group if they have had one or more secondary care consultations or if they have had any antenatal admissions to hospital.

- Women who have had a General Practitioner, private obstetrician, or secondary care team as their LMC.

Outcomes

- Antepartum stillbirth: Antepartum stillbirth rates will be calculated as the number of fetal deaths that occur before the onset of labour divided by the total number of births in our cohort.

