1. EXPOSURE

For classifying the exposure status LMC data will be collected from individual DHBs. This category is the only one not available from the MOH who only hold LMC data for around 70% of women.

It is difficult to know how robust/complete the DHB data is before accessing it. Generally it is entered by clinicians. The available categories are as follows:

- LMC data:

LMC at booking

LMC at admission in labour

Labour care provided by*

Delivered by

Labour and delivery assisted by

*The last three are not collected by all the DHBs.

- Data to classify ‘medical input’:

A woman will be classified as having medical input if she has had antenatal secondary care consultations. This data is held by the MOH and comes from the National Non- Admitted Patient Collection. We will analyse the number of secondary care consultations and the type of consultation. The following codes are relevant:

| W03002 | First obstetric consults |
| --- | --- |
| W03003 | Subsequent obstetric consults |
| W03005 | Amniocentesis |
| W03006 | Chorion villis sampling |
| W03007 | Rhesus Clinics - multidisciplinary clinics |
| W03008 | Maternity foetal medicine clinics - multidisciplinary clinics |
| W03009 | Foetal medicine / anomalies clinics - multidisciplinary clinics |

Some of these categories are more likely to be associated with greater obstetric input; number of consults is also relevant. For example a woman who has one consult recorded under amniocentesis and no further consults likely had a negative test and limited obstetric input in her care. Sub-category analysis will therefore be necessary.

The number of obstetric related hospital admissions within the pregnancy is also available from the NMDs. These data are not detailed and we will be making the assumption that if a patient has been admitted to hospital she will have had some level of secondary care input. Again number of admissions is relevant and sub-category analysis necessary.

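### For antepartum stillbirth the medical-input comparison is open to reverse causation, because contacts prompted by the death can define the exposure

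*SAP*

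**What the plan says.** **Outcome.** Under Outcomes, the antepartum stillbirth rate is the "number of fetal deaths that occur before the onset of labour divided by the total number of births in our cohort".

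**Exposure.** Under Exposure, the reference group is women with a "midwife as Lead Maternity Carer at booking and at admission in labour and where there is no evidence of medical input". A woman with a midwife LMC goes into the medical-input group after "one or more secondary care consultations or if they have had any antenatal admissions to hospital". A separate group holds women whose LMC is a GP, a private obstetrician or the secondary care team.

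**Data rules.** Available data, 1. EXPOSURE, repeats the consultation rule: "A woman will be classified as having medical input if she has had antenatal secondary care consultations". For admissions it says: "The number of obstetric related hospital admissions within the pregnancy is also available from the NMDs". It grants that these records lack detail and assumes that "if a patient has been admitted to hospital she will have had some level of secondary care input".

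**Analysis.** Incidence of every outcome is to be reported overall and by group. Logistic models then compare shared with midwife-only care for each outcome the SAP calls major, without listing which those are.

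**The concern.** Exposure is ascertained over the whole pregnancy, and an antepartum death falls inside that window. No rule says that a consultation or admission must come before the death, or that a contact made because of the death is disregarded. LMC at admission in labour is recorded later still. A woman who was under midwife-only care until the fetus died can therefore lose that label because it died.

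Each such death leaves the midwife-only numerator. If the woman keeps a midwife LMC, the death is added to the medical-input numerator. If the secondary care team has become her LMC by labour, it is added to the third group. Either way the midwife-only rate falls for a reason unrelated to the quality of care.

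The distortion favours midwife-only care. The Background says that reassuring results would be used to defend the current model, and that results like those of the Dutch study would prompt further research. A bias that can create reassurance or hide an excess matters for both uses.

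**Working it through.** **1. Order of events.** For an antepartum stillbirth, set side by side when each item is fixed:

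- Outcome: before the onset of labour.
- Consultations and admissions: any time in the pregnancy, so before or after the death.
- LMC at booking: before the death.
- LMC at admission in labour: after the death.

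Only LMC at booking is certain to precede the outcome.

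**2. Do the planned safeguards cover this?** The covariates describe the woman and the birth; none records whether a contact came before or after the death. Low birth weight is a negative control for confounding, and a label triggered by a death would not show in it. The sub-category analyses in Available data, 1. EXPOSURE, split by number and type of consultation and by number of admissions, not by date or reason.

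**3. Size.** The SAP gives no stillbirth rate, no expected share with medical input and no figure for relabelling, so there is no planned figure to reproduce. The inputs below are assumptions:

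- b: share of women in the two midwife-LMC groups with genuine earlier input, 0.3 or 0.4.
- x: share of otherwise midwife-only stillbirths relabelled because of the death, 0.10, 0.25 or 0.50.
- True odds ratio 1, rare outcome.

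If all relabelled deaths move to medical input, the odds ratio (medical input v midwife-only) is approximately

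OR = [1 + x(1 − b)/b] / (1 − x).

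If they all move to the secondary-care LMC group, the medical-input rate is unchanged and OR = 1/(1 − x).

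Worked case, b = 0.4 and x = 0.25: of 100 stillbirths, 40 belong to medical input and 60 to midwife-only. Relabelling moves 0.25 × 60 = 15, giving 55 and 45. Then OR = (55/40)/(45/60) = 1.375/0.75 = 1.83. If the 15 go to the third group, OR = (40/40)/(45/60) = 1.33.

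| x | b = 0.4, to medical input | b = 0.3, to medical input | To secondary-care LMC |
|---|---|---|---|
| 0.10 | 1.15/0.90 = 1.28 | 1.233/0.90 = 1.37 | 1/0.90 = 1.11 |
| 0.25 | 1.375/0.75 = 1.83 | 1.583/0.75 = 2.11 | 1/0.75 = 1.33 |
| 0.50 | 1.75/0.50 = 3.50 | 2.167/0.50 = 4.33 | 1/0.50 = 2.00 |

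**4. Would it show at the planned size?** Doubling 48 878 gives 97 756 births. Assume all are in the two midwife-LMC groups, b = 0.5, and 2 antepartum stillbirths per 1000. A true null then appears as OR 1.22 (95% CI 0.92–1.62) at x = 0.10 and 1.67 (1.25–2.23) at x = 0.25. The interval excludes 1 in the second case but not in the first.

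**5. Could it mask a real excess?** The only effect size the SAP prints is a relative risk of 2.33, for a different endpoint in the Dutch study. Used purely as an illustration with b = 0.5, the observed midwife-only v medical-input ratio is about (1 − x) × 2.33/(1 + 2.33x). At x = 0.25 this is 1.7475/1.5825 = 1.10, and at x = 0.40 it is 1.398/1.932 = 0.72.

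**The case against.** **Stated fairly, and it stands.** The size rests wholly on x, which the SAP does not give. The routes may be narrower than they look. The text speaks of antenatal admissions and does not say whether the admission that ends in delivery of a stillborn baby is one. Nor does it say whether an assessment for suspected fetal death would carry one of the listed consultation codes. A stillbirth odds ratio is not explicitly promised either: the outcomes called major are not listed, and objective iii compares only where relevant. Group-specific incidence is planned for every outcome, however, and those rates carry the same distortion.

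**Partial mitigation.** Separating women with a single contact may isolate some death-prompted contacts, but it cannot tell them from genuine single consultations.

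**Stronger readings that a reader might infer, and that the documents do not support:**

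- That the comparison *is* reverse-causal. The definitions permit this but do not show how often it happens.
- That a contact for reduced movements before the death is the same problem. Such a contact precedes the outcome and is genuine input; any resulting bias is confounding by indication.
- That longer pregnancies have more time to acquire a contact (immortal time), adding to the bias. An early death cuts short the time to acquire a contact and so tends to stay in the midwife-only group, which works in the opposite direction.
- That the exposure definition fails for every outcome. For intrapartum and neonatal outcomes, antenatal contacts already precede the event. Discarding late contacts there would relabel women with real late input as midwife-only.

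**Conclusion.** The point holds for antepartum stillbirth alone. As written, exposure is ascertained over a window that contains the outcome and runs past it, and nothing else in the SAP puts contact before death. The direction is clear for relabelled deaths: it lowers the midwife-only rate. With genuine input assumed at 30–40%, a true null could appear as an odds ratio between 1.11 (10% relabelled, all to the secondary-care LMC group) and 4.33 (50% relabelled, all to medical input). These figures illustrate sensitivity and do not predict the result, since neither the share relabelled nor its destination can be taken from the SAP. The rule should be settled before this outcome is compared between groups.

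**What to change.** For antepartum stillbirth only:

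- Classify LMC by LMC at booking. The SAP lists this field and does not flag it as missing at some DHBs.
- Do not count consultations or admissions on or after recognition of the fetal death. State that this includes the admission ending in the stillbirth delivery.
- Add a sensitivity analysis with a landmark that counts only contacts before 37+0 weeks.
- If contact dates or the date of recognition of death cannot be obtained, report this outcome by booking LMC or descriptively, without a medical-input odds ratio.

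Leave the exposure definition for the other outcomes unchanged.

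The cost is a short wording change, a date filter on consultation and admission records, and the loss of some late contacts for this one outcome. Whether the dates exist has to be checked: the SAP itself calls the admission data not detailed, and it names no source for the date on which death was recognised.

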**What impact does the New Zealand maternity care model have on fetal and neonatal outcomes? A retrospective cohort study comparing exclusive midwife led care with a shared care model.**

Background

New Zealand has a maternity system that has undergone a number of changes in the past twenty years that have moved it away from a medical model of care and towards a midwifery model [18]. The changes have been the subject of scrutiny and controversy focusing on questions related to the safety of the system [3, 5, 6, 7, 15, 16, 17, 20, 22]. Despite this, there has been little in the way of systematic evaluation that specifically relates to the safety of the maternity system [8, 10-14, 19].

New Zealand’s maternity system is based on a midwife-led care model, whereby midwives practice with a level of autonomy higher than most of their overseas counterparts [9, 21, 23]. International literature has generally supported the safety of the midwife-led care model [4]. However this does not provide sufficient evidence to support the safety of the New Zealand system, as in many countries where the international literature was based midwives have less autonomy than they do in New Zealand; so even in midwife-led births there is some medical input. The uniqueness of our system means that evaluation of the safety of New Zealand based midwife-led care needs to be addressed within New Zealand.

Along with the lack of New Zealand based research, impetus for research in this area has been provided by a recently published Dutch study [1]. Holland has a maternity system that is similar to ours in that midwives practice with a high level of autonomy; therefore evaluation in a Dutch context is relevant to us. The Dutch study found, most significantly, that “*infants of pregnant women at low risk whose labour started in primary care under the supervision of a midwife had a significant higher risk of delivery related perinatal death than infants of pregnant women at high risk whose labour started in secondary care under the supervision of an obstetrician… relative risk 2.33*” [1, p. 1]. Given the similarities between the Dutch maternity system and ours, this is a concerning finding in the New Zealand as well as Dutch context.

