In contrast, further incentive for addressing the lack of New Zealand based research is provided with the demonstrated value of midwifery led care. Consumer satisfaction surveys have reported high levels of support for our current model [6]. The most recent (2011) survey reported on 3225 women; 89% of these women reported feeling satisfied or very satisfied with the care they received from their LMC. This is encouraging in terms of midwife-led care as three quarters of respondents were registered with a self-employed midwife as their LMC [6].

However, the media, consumer and professional opposition may have led to a decrease in women’s confidence of the system and has been reported as being discouraging to midwives [2]. Midwives have not had an evidence base to defend the current model, which has exacerbated the critique. If evidence can be produced that provides support for the safety of the current maternity system, then this can be used by midwives to defend their profession, and to generate support, and increase consumer confidence.

If however the study finds similar results to the Dutch study, in that midwife-led care leads to poorer outcomes for babies compared with medical care, this evidence can be used as incentive to generate further research that focuses on the reasons for this, with the aim to alleviate the causes and improve outcomes for babies.

Ultimately a safer maternity system that supports the best possible outcomes for babies is an important goal. Midwifery care is an essential part of our maternity system and it is essential for its continuation that it be based on evidence with its safety ensured.

Aim

This study aims to evaluate key aspects of the safety of the New Zealand maternity system. Specifically we will investigate serious fetal and neonatal outcomes that are potentially related to care provider.

Objectives

i) To review the literature regarding the safety of midwife-led care models within New Zealand and internationally.

ii) To demonstrate what data is available for the purpose of reviewing safety related fetal and neonatal outcomes in relation to maternity care provider, within New Zealand.

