- Intrapartum mortality: Intrapartum mortality rates will be calculated as the number of fetal deaths that occur after the onset of labour but before delivery divided by the total number of births in our cohort, not including antenatal still births.
- Early neonatal mortality: Early neonatal mortality rates will be calculated as the number of early neonatal deaths, that is deaths that occur post-delivery and within seven days of life, divided by total number of births in our cohort, not including antenatal still births or babies who have died in the intrapartum period.
- Neonatal admission to a specialist neonatal unit: Neonatal admission rates will be calculated as the number of babies admitted to a specialist neonatal unit within the first seven days of life divided by the total number of births in our cohort but not including antenatal stillbirths, or babies dying intrapartum, or in the early neonatal period.
- Low Apgar score: Rates of low Apgar score will be calculated as the number of babies born with an Apgar score at five minutes post-delivery of below seven, divided by total number of births in our cohort, not including antenatal still births or babies who have died in the intrapartum period.
- Birth related asphyxia: Rates of birth related asphyxia will be calculated based on the number of babies identified with the condition by ICD-10-AM codes P210, P211, P219, divided by total number of births in our cohort, not including antenatal still births or babies who have died in the intrapartum period.
- Intrauterine hypoxia: Rates of intrauterine hypoxia will be calculated based on the number of babies identified with the condition by ICD-10-AM codes P200, P201, P209 divided by total number of births in our cohort, not including antenatal still births or babies who have died in the intrapartum period.
- Hypoxic ischaemic encephalopathy: Rates of hypoxic ischaemic encephalopathy will be calculated based on the number of babies identified with the condition by ICD-10-AM code P916, divided by total number of births in our cohort, not including antenatal still births or babies who have died in the intrapartum period.

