- Low birth weight: Where the birth weight was recorded as less than 2500 grams. This variable was included as a negative control outcome in order to determine whether adjustment for confounding for the main outcomes was likely to have been sufficient. This is on the assumption that model of care is unlikely to substantially affect birth weight directly, but similar confounders may affect the relation between low birth weight, model of care and the outcomes

Covariates

The study will collect a number of maternal variables that may be potential confounders or mediators. These include:

- Maternal age: 12-18 yrs; 19-25 yrs; 26-35 yrs; 36-40 yrs and 40+.
- Ethnicity: NZ European, Māori, Pacific Island, Asian, Other.
- Deprivation: NZ Dep quartiles.
- Parity before delivery: 0, 1, 2, 3, 4+.
- Gestation at delivery: 37/40-38/40; 39/40-40/40; 41/40; 42+ weeks.
- Location of delivery: Primary birthing unit, secondary or tertiary hospital.
- Mode of delivery: Normal vaginal delivery, instrumental delivery, caesarean section.
- Pre-existing diabetes and/or hypertension: yes, no.

Analysis

- We will first calculate incidence rates (and 95% confidence intervals) of all outcomes for all groups combined and then for each group separately.
- We will then develop logistic regression models to calculate odds ratios (and 95% confidence intervals) for each major outcome comparing women receiving shared compared with midwife only care. The models will include potentially confounding patient characteristics such as age, parity, ethnicity and presence of pre-existing conditions.

Available data

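### The neonatal-unit admission rate is defined on first-week survivors only, so babies admitted and then dying within seven days are dropped or fall outside the denominator

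*SAP*

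**What the plan says.** All the relevant text is in the SAP, mainly under Outcomes.

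- **Admission, numerator:** "the number of babies admitted to a specialist neonatal unit within the first seven days of life". No exclusion is attached to this count.
- **Admission, denominator:** births in the cohort, "but not including antenatal stillbirths, or babies dying intrapartum, or in the early neonatal period".
- **Early neonatal death:** "deaths that occur post-delivery and within seven days of life". This is the same window as the admission outcome.
- **Low Apgar score, birth related asphyxia, intrauterine hypoxia, hypoxic ischaemic encephalopathy:** the denominator is births, "not including antenatal still births or babies who have died in the intrapartum period". Early neonatal deaths stay in.
- **Analysis:** after the incidence rates, the SAP plans "logistic regression models to calculate odds ratios (and 95% confidence intervals) for each major outcome". It does not list which outcomes are major.
- **Aim:** "we will investigate serious fetal and neonatal outcomes that are potentially related to care provider". Early neonatal mortality is one of the listed outcomes, so the plan itself treats it as something the model of care might affect.

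**The concern.** The three mortality denominators narrow for a sound reason. A baby who died before labour cannot die in labour, and one who died in labour cannot die after delivery. That reasoning does not carry over to admission. A live-born baby who dies on day 3 was at risk of admission from birth, and any admission came before the death that triggers the exclusion. Restricting to first-week survivors therefore conditions on an event that follows exposure and may depend on it.

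Two things follow. The admission rate omits babies who are likely to be among the most severely ill of those admitted. And if early neonatal mortality differs between care groups, the group with more deaths loses more admissions and looks slightly better on this outcome. The rates also stop being comparable: a baby with hypoxic ischaemic encephalopathy who is admitted and dies within the week counts for that diagnosis but not for admission.

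**Working it through.** **Plan's own figure.** There is none to reproduce. The SAP states no admission rate and no early neonatal death rate, and its sample size (48 878, to be doubled) is built on intrapartum death. All rates below are assumptions.

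**Step 1: the two readings of the definition.**

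| Reading | Numerator | Denominator | Consequence |
|---|---|---|---|
| Literal | all admissions within 7 days | survivors of the first week | numerator not a subset of denominator; cannot be fitted as a logistic model |
| Proper proportion or logistic model | admissions among survivors | survivors of the first week | admitted babies who die are dropped |

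The second reading is the workable one and is used in Steps 2 to 4.

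**Step 2: share of admissions lost.** Let *e* be the early neonatal death risk, *f* the share of those babies admitted before death, and *a* the admission rate among all live births. The share lost is *e* × *f* / *a*. Assumed ranges: *e* 0.3 to 1.0 per 1000, *f* 50% to 80%, *a* 2% to 4%.

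- Smallest: 0.0003 × 0.5 / 0.04 = 0.4%
- Largest: 0.001 × 0.8 / 0.02 = 4%

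**Step 3: effect on the odds ratio when true admission is equal.** The rate after exclusion is (*a* − *f* × *e*) / (1 − *e*) in each group. The ratio of deaths between groups is set near the one figure the SAP cites, "relative risk 2.33", which is for delivery-related perinatal death in the Dutch study and is borrowed here for illustration only.

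Worked case: *e* = 1.4 v 0.6 per 1000 (ratio 2.33, mean 1.0 with equal groups), *f* = 80%, *a* = 2%.

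- Higher-death group: (0.02 − 0.00112) / 0.9986 = 1.891%
- Lower-death group: (0.02 − 0.00048) / 0.9994 = 1.953%
- Odds ratio: 0.967, where the true value is 1

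| Early deaths per 1000 | Admitted before death | OR at 2% admission | OR at 4% admission |
|---|---|---|---|
| 1.4 v 0.6 | 80% | 0.967 | 0.984 |
| 1.0 v 0.43 | 80% | 0.977 | 0.989 |
| 0.3 v 0.13 | 50% | 0.996 | 0.998 |
| equal | any | 1.00 | 1.00 |

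**Step 4: wider assumptions, seen from the other side.** Now let admission be equal among survivors, at 2% to 8%, with a death ratio of 2.33 and 50% to 90% of dying babies admitted first. With the deaths excluded the odds ratio is 1.00. With them restored it is 1.004 to 1.06 when the lower-risk group has 0.5 to 1 deaths per 1000. It reaches 1.11 only at the extreme corner (2 per 1000, 2% admission, 90% admitted).

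**Step 5: comparison with sampling error.** Doubling 48 878 gives 97 756, or 48 878 per group if two equal groups are assumed. The standard error of the log odds ratio at the null is √(2 / (*n* × *a* × (1 − *a*))).

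- *a* = 2%: 0.0457, so 95% limits of 0.914 to 1.094
- *a* = 4%: 0.0326, so 95% limits of 0.938 to 1.066

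The shifts in Step 3 lie inside these limits.

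**The case against.** The case for leaving the text alone has real content.

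- **The effect is small.** It needs a difference in early mortality to exist at all, and on the assumed rates it is within sampling error. This stands, and it limits the weight of the point.
- **Early deaths are reported anyway.** They form a separate outcome on the live-born denominator. A reader might infer that the exclusion conceals harm; the document does not support that, because excess deaths would show in the mortality outcome. Reporting them there does not, however, correct the admission rate or its odds ratio.
- **The direction is not tied to one model of care.** A reader might infer that the rule favours midwife-only care. Nothing in the SAP says which group will have more early deaths. The women with medical input or a medical lead carer may be at higher risk, in which case the exclusion would favour them.
- **Removal from the numerator is not written.** A reader might take it as stated. The sentence attaches the exclusion to the denominator; removal is implied by a proper proportion or by the logistic model. The literal alternative is not a valid proportion, so the definition needs correcting either way.
- **Apgar score and asphyxia are imperfect comparators.** They are fixed at or near delivery, before early death can intervene. This is fair. Hypoxic ischaemic encephalopathy is the closest comparator, and it keeps early deaths.
- **Admission among survivors is a definable quantity.** It is, but the SAP does not say that it wants it or why, and it departs from the denominator of the other four morbidity outcomes.

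**Conclusion.** The definition is faulty as written. It excludes first-week deaths from the denominator of an outcome counted over that same week, without a reason and unlike the other four neonatal morbidity outcomes. On the workable reading it conditions on survival; on the literal reading the ratio is not a proportion.

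The size is modest. Under the assumed rates the admission count is understated by 0.4% to 4%. If early mortality differs between care groups by a ratio of about 2.33, the odds ratio is biased by about 0% to 3% in favour of the group with more deaths. With equal early mortality there is no material bias in the odds ratio, though the incidence rate still omits these admissions. These figures rest on assumed death rates, admission rates and shares admitted before death. The more extreme assumptions in Step 4 give larger shifts. The point deserves correction because the repair is nearly free, not because it is likely to change a conclusion.

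**What to change.** In the admission outcome, replace the denominator with the one already used for the low Apgar score and the other neonatal diagnoses: "divided by total number of births in our cohort, not including antenatal still births or babies who have died in the intrapartum period". Add that every admission within seven days counts, including babies who later die, and that the same set of babies supplies numerator, denominator and logistic model.

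Optionally, report admission or early neonatal death as a sensitivity outcome. On the live-born denominator a baby who dies before being admitted counts as a non-event, and the combined outcome prevents that from reading as a good result.

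If the investigators do want admission among first-week survivors, the SAP should say so, give the reason, and restrict the numerator explicitly.

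The cost is about one line of text. Admission and early death are both already collected, so no new data are needed.

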1. OUTCOMES

Outcomes are also collected from the MOH’s NMDS. We may need to use the Perinatal Maternal Mortality Review Committee Data to ascertain antepartum vs. intrapartum stillbirth as MOH data may not be sufficiently detailed.

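### The low-Apgar rate keeps live-born babies with no recorded score in its denominator, so they count as not low; the denominator should be babies with a recorded score

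*SAP*

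**What the plan says.** In the SAP's Outcomes section, the low-Apgar rate is given by this formula: "number of babies born with an Apgar score at five minutes post-delivery of below seven, divided by total number of births in our cohort". The exclusions are worded separately: "not including antenatal still births or babies who have died in the intrapartum period". Those two exclusions are the only ones, which leaves all live births.

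Low birth weight, listed in the same section as a negative control outcome, is defined as "Where the birth weight was recorded as less than 2500 grams". No denominator is given for it.

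The Analysis section then says: "We will first calculate incidence rates (and 95% confidence intervals) of all outcomes for all groups combined and then for each group separately". After that the plan is to "develop logistic regression models to calculate odds ratios (and 95% confidence intervals) for each major outcome comparing women receiving shared compared with midwife only care". It does not say how a baby with a blank outcome enters either step.

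Under Available data, outcomes come from the health ministry's routine national dataset. The SAP does not say how complete the five-minute Apgar field is, and it plans no count of missing scores by group.

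**The concern.** An Apgar score is a measured value, so a blank is not a normal result. This separates it from the asphyxia, hypoxia and encephalopathy outcomes, which share the same denominator but are identified by diagnosis codes. For those, treating no code as no diagnosis is the usual convention.

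Three consequences follow.

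- Every reported low-Apgar rate is pulled down by that group's missing share.
- If recording differs by care model, the crude comparison favours the group with poorer recording. The Covariates section shows births ranging from primary units to tertiary hospitals, so different recording is plausible, though the SAP does not show it.
- The rate table and the logistic models may use different babies, because only the rate has a stated denominator.

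Nothing in the plan would bring any of this to light, since missing scores are not to be counted.

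**Working it through.** **Inputs from the SAP.** The numerator needs a score below seven. The denominator is all births less antenatal stillbirths and intrapartum deaths. The SAP gives no Apgar rate and no missing share, so there is no figure of its own to reproduce. All risks and missing shares below are assumptions.

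**Step 1: effect on a rate.** Let p be the low-Apgar risk among recorded babies and m the share with no score. The rate as defined is p(1 − m). With recorded babies as the denominator it is p. At p = 1.5% and m = 5%, the defined rate is 1.5% × 0.95 = 1.425%.

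**Step 2: effect on the crude ratio.** Assume scores are missing at random and there is no true difference. The ratio of the better-recorded to the worse-recorded group is (1 − m_better)/(1 − m_worse).

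| Missing, worse v better recorded | Ratio as defined | Ratio, recorded only |
|---|---|---|
| 5% v 5% | 0.95/0.95 = 1.00 | 1.00 |
| 2% v 1% | 0.99/0.98 = 1.01 | 1.00 |
| 5% v 1% | 0.99/0.95 = 1.04 | 1.00 |
| 10% v 1% | 0.99/0.90 = 1.10 | 1.00 |

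**Step 3: effect on the odds ratio.** If blanks are coded as not low, the odds ratio moves by almost the same amount. At a true risk of 1% and 5% v 1% missing, (0.0099/0.9901)/(0.0095/0.9905) = 1.043. If blanks are dropped, it stays at 1.00.

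**Step 4: scale against precision.** The SAP says "An adequately powered simple study requires a sample size of 48 878" and plans to double this, giving 97,756. Assume two equal groups of 48,878 and a 1.5% risk. That is about 733 events per group, and the standard error of the log ratio is √[2 × (1 − 0.015)/733] ≈ 0.052. The 1.04 artefact is ln(1.042) = 0.041, about 0.8 standard errors. The 1.10 artefact is ln(1.10) = 0.095, about 1.8 standard errors.

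**Step 5: when missingness depends on the score.** Assume 1.5% low among recorded babies, 10% low among unrecorded babies, and 5% v 1% missing.

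- True rates: 0.95 × 1.5% + 0.05 × 10% = 1.925%, and 0.99 × 1.5% + 0.01 × 10% = 1.585%. The ratio is 1.585/1.925 = 0.82.
- As defined: 1.425% and 1.485%, ratio 1.04.
- Recorded only: 1.5% and 1.5%, ratio 1.00.

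The total distortion on the log scale is ln(1.042/0.823) = 0.236. Of this, ln(1.00/0.823) = 0.194, about 82%, remains with the recorded-only denominator. The rule itself adds only the step from 1.00 to 1.04.

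**Step 6: the low-then-normal check in the same example.** Counting all unrecorded scores as low gives (1.485% + 1%)/(1.425% + 5%) = 2.485/6.425 = 0.39. Counting all as normal gives 1.04. In this example the range contains the true 0.82.

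**The case against.** The strongest reply is that the SAP never says a missing score counts as normal. The same denominator wording serves early neonatal death and the coded diagnoses, so it may be meant only to say who is at risk, with the handling of blanks left open. That may well be the intent. But the text gives an explicit formula, and anyone who follows it gets the rate in Step 1.

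The other objections largely stand and limit the point.

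- **No missingness is shown.** The SAP's caution about completeness concerns the carer data held by the District Health Boards. For outcomes, its only doubt is whether antepartum and intrapartum stillbirth can be told apart.
- **A reader might infer that the adjusted group comparison is biased.** The SAP does not support this. That comparison is made by logistic regression, with no rule for blanks. If they are dropped, the denominator rule affects only the descriptive rates.
- **A reader might blame the rule for a true 0.82 appearing as 1.04.** Step 5 shows that most of this comes from the assumed link between missingness and score.
- **A reader might infer that missing birth weights are already counted as normal, so that the negative control is biased.** With no denominator stated, that does not follow; the rule is simply unstated.
- **Low Apgar cannot be called one of the commoner outcomes from this document.** It says only that intrapartum fetal death is the rarest.

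**Conclusion.** The definition as written counts unrecorded live-born babies as not low and understates each group's rate by its missing share. That much follows from the text alone.

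The effect on the crude comparison is conditional. It is nil with equal missingness; under missing at random it is 1.04 at 5% v 1% and 1.10 at 10% v 1%. These shares are assumed, and the real size is unknown until missing scores are counted. On the assumed equal split and 1.5% risk, the artefact ranges from under one to nearly two standard errors, and a larger sample would not remove it. The odds ratios are affected only if blanks are coded as normal; otherwise the inconsistency is between the rate table and the models.

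This is a modest, inexpensive correction to a stated formula. It is not evidence that the care-model comparison is biased, and it does not touch the sample size.

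**What to change.** 1. Under Low Apgar score, make the denominator live-born babies with a recorded five-minute score.
2. In the Analysis section, state that the rate and the logistic model use the same babies.
3. Report the number and share of unrecorded scores in each exposure group.
4. Add a check that counts unrecorded scores as low and then as normal, because the recorded-only denominator does not remove bias when missingness depends on the score. Both settings apply one assumption to all groups, so present them as a sensitivity range and not as strict limits.
5. State the matching denominator for low birth weight, namely babies with a recorded weight, so that the two measured outcomes follow one convention.

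The cost is about one sentence per outcome, one column in the rate table and two extra model runs. The denominator becomes slightly smaller. The missing-score counts also serve the SAP's own objective of showing what outcome data are available.
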